| 
Statistical Analysis.
 
Primary immunogenicity endpoint is the titer of antibodies binding to the SARS-CoV-2 S protein on 14th day measured by immunoassay.
 
Secondary immunogenicity endpoint is NAV (FRNT50 GMT, which represent the reciprocal dilution of serum that neutralizes 50% of the input virus expressed as the geometric mean) evaluated in the randomization visit (previously COMIRNATY vaccination) and on 14, 28 days and 3, 6 and 12 months after dosing.
 
Primary statistical analysis will be performed on day 14th after randomization.
 
Main comparisons are:
                                                                                                                                                                                                                                                                                                                                                                                                                                                                                                                                                                                                                                                                                                                                                                                                                                                                                                                                                                                                                                                                                                                                                                                                                         |                                                                                                                                         |

- Immune response measured by immunoassay on 14 days after the randomization ( $\pm 2$  days).

Other comparisons will include:

- Immune response (antibodies against SARS-CoV-2 spike protein) measured by immunoassay at 7 days after the randomization ( $\pm 2$  days).
- Immune response (antibodies against SARS-CoV-2 spike protein) measured by immunoassay at 28 days after the randomization ( $\pm 2$  days)
- Immune response measured by NAV at 14 days after the randomization ( $\pm 2$  days).
- Immune response measured by NAV at 28 days after the randomization ( $\pm 2$  days)
- Correlation of immune response measured by NAV and immunoassay (antibodies against SARS-CoV-2 spike protein).
- Change in immune response from baseline (randomization visit) to 14 and 28 days after COMIRNATY vaccination in the immediate and control groups.
- Differences in immune response at the different time points by both immunoassay (antibodies against SARS-CoV-2 spike protein) and NAV tests.
- Percentage of patients reaching a FRNT50 GMTs  $>1000$  at 14 and 28 days (or the figure having best evidence in the literature at the time of analysis)
- Maintaining a FRNT50 GMTs  $>1000$  (or the figure having best evidence in the literature at the time of analysis) at 3, 6 and 12 months.

A full description of statistical analysis will be made in the SAP.

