| Trial Overview:               | 
Design
 
This is a randomized, non-blinded, controlled, adaptive, multicenter, Phase II study in subjects aged <math>\geq 18</math> years and in good health or stable clinical situation that have received a previous single dose of VAXZEVRIA.
 
This is a phase 2 adaptive trial developed to evaluate the immunogenicity of a dose of COMIRNATY after a previous single dose of VAXZEVRIA. A stratification will be made based on the following factors: study site, sex and age. This protocol allows to test the immunogenicity and safety of a heterologous vaccination strategy after a previous single dose of VAXZEVRIA.
 
Subjects will be randomized to immediately receive or not a dose of COMIRNATY in a ratio of 2:1.
 
If primary analysis at 14 days confirms the starting hypothesis, subjects randomized to no vaccination will be considered for administration of one dose of COMINARTY at day 28th according to Public Health Department of the Ministry of Health recommendations on heterologous vaccination. If vaccinated, subjects will be followed at the time points defined in the flowchart.
 
In case the primary analysis does not confirm the starting hypothesis, subjects will be followed at the time points defined in the flow-chart without administration of COMIRNATY.
 
In case Public Health Department gave instructions to give the second dose of VAXZEVRIA to those subjects having received the first dose, subject will be followed as indicated in flowchart of Group 2.
 
Other heterologous vaccination strategies could be incorporated if deemed necessary for public health reasons. This could include the use of different vaccination strategies including those already marketed vaccines for comparative assessment of their safety and efficacy on SARS-CoV-2 and its variants.
 
The different intervention arms planned (and its corresponding control arm) can be carried-out in different trial sites, thus not all trial sites must participate in all arms. See trial schematic for more details.
 |

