| Randomization and blinding    | 
Randomization.
 
A central randomization stratified by study site and age will be used.
                                                                                                                                                                                                                                                                                                                                                                                                                                                                                                                                                                                                                                                                                                                                                                                                                                                                                                                                                                                                                                                                                                                                                                                                                                                                                                                                                                                                                                                                                                                                                                                                                                                                                                                                                                                                                                                                                                                                                                                                                               |

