## **4. Study Design**

### **4.1. Overall Design**

This is a randomized, non-blinded, controlled, adaptive, multicenter, Phase II study in subjects aged more than 18 years and in good health or stable clinical situation that have received a previous single dose of VAXZEVRIA.

This is a phase 2 adaptive trial developed for evaluating the immunogenicity of a dose of COMIRNATY after a previous single dose with VAXZEVRIA. A stratification will be made for the following factors: site of vaccination, sex and age. This protocol allows to test the immunogenicity and safety of a heterologous vaccination strategy after a single dose of VAXZEVRIA.

Subjects will be randomized to immediately receive or not dose of COMIRNATY in a proportion of 2:1.

If primary analysis at 14 days confirms the starting hypothesis, subjects randomized to no vaccination will be considered for administration of one dose of COMINARTY at day 28th according to Public Health Department of the Ministry of Health recommendations on heterologous vaccination. If vaccinated, subjects will be followed at the time points defined in the flowchart.

In case the primary analysis does not confirm the starting hypothesis, subject will be followed without administration of COMINARTY.

In case Public Health Department gave instructions to give the second dose of VAXZEVRIA to those subjects having received the first dose, subject will be followed as indicated in flowchart of Group 2.

Other heterologous vaccination strategies could be incorporated if deemed necessary for public health reasons. This could include the use of different boost strategies including those already marketed vaccines for comparative assessment of their safety and efficacy on SARS-CoV-2 and its variants.

The different intervention arms planned (and its corresponding control arm) can be carried-out in different trial sites, thus not all trial sites must participate in all arms.

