#### **Randomisation and blinding:**

- Randomization will be centralized, and each participant will be randomized stratified by age and centre. Randomization will be in a proportion of 2:1 (COMIRNATY:No vaccination)
- This is an open-label trial.

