### **6.3. Measures to Minimize Bias: Randomization**

This is an open-label clinical trial.

The randomization list will be generated using software SAS 9 for Windows. The randomization list will be imported into the REDCap program so the researchers can randomize candidate subjects using an easier-to-use interface. Subjects that meet the selection criteria will be randomized in a 2:1 ratio between the two treatment groups (Intervention arm: administration of a COMINARTY boosted dose vs Control arm: no administration of boosted dose), stratifying by center, gender and age (18-49 years, 50-59 years and  $\geq 60$  years), in order to achieve balanced randomization in the two treatment groups. The assignment of treatment to each subject will be centralized, keeping the sequence hidden.

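### The protocol disagrees with itself on whether sex stratifies the randomisation, and its primary t-test uses none of the stratification factors

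*Protocol*

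**What the plan says.** Two statements leave sex out, and both are explicitly about randomisation:

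- Section 1.1, Randomization and blinding: "A central randomization stratified by study site and age will be used".
- Section 4.1, Randomisation and blinding: "Randomization will be centralized, and each participant will be randomized stratified by age and centre".

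Three statements include it:

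- Section 6.3: "stratifying by center, gender and age", with age in bands 18-49, 50-59 and 60 or over. This section says the list is generated in SAS and imported into REDCap, and gives balance between the arms as the purpose.
- Section 1.1, Trial Overview: "A stratification will be made based on the following factors: study site, sex and age".
- Section 4.1, Overall Design: "A stratification will be made for the following factors: site of vaccination, sex and age".

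Section 9.3.2 compares the arms on day-14 titre by a one-tailed t-test on the log scale, with a rank test as fallback. It names no covariate or stratum. Section 9.3.3 uses the same method for the secondary immunogenicity endpoints. Section 9.3.4 rules out subgroup analyses. Section 9 leaves technical detail to the SAP.

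**The concern.** The randomisation list either balances sex within centre and age band or it does not. The protocol supports both answers, and sections 1.1 and 4.1 each contain both, so this is not simply a short summary set against a fuller text. A monitor or reader cannot tell from the protocol whether the list in use conforms to it. An analyst who wants to respect the design does not know which factors constrained allocation.

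There is a second, linked matter. Whichever factors were used, the stated primary test discards them. Stratified allocation removes part of the chance variation between arms. An unadjusted standard error still counts that variation, so the design pays for balance that the analysis does not use.

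**Working it through.** **1. Can the five statements be reconciled?**

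| Place | Site/centre | Age | Sex | Says randomisation? |
|---|---|---|---|---|
| 1.1 Trial Overview | yes | yes | yes | no, only a stratification |
| 1.1 Randomization | yes | yes | no | yes |
| 4.1 Overall Design | yes | yes | yes | no, only a stratification |
| 4.1 Randomisation and blinding | yes | yes | no | yes |
| 6.3 | yes | yes, 3 bands | yes | yes |

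One could take the two general statements to mean the sampling of participants. But the Selection sample paragraph in section 4.1 stratifies the sampling by age group and does not mention sex. Even with those two statements set aside, the second and fourth rows conflict with the last, and all three describe randomisation. Strata per centre: 3 without sex, 3 × 2 = 6 with it.

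**2. Scale of the endpoint.** Section 9.5 gives a coefficient of variation (CV) of 1.2 and a ratio of 1.35. The log-scale SD is √ln(1 + 1.2²) = √0.892 = 0.944. To confirm that this is the plan's scale: 1.5 × [0.944 × (2.576 + 0.842) / ln 1.35]² = 173.506 (unrounded inputs), which is the tabled control-arm size. The match needs the two-sided 0.01 quantile; the one-sided quantile named in the text gives 149.098. That is a separate matter. Stratification does not enter the sample size.

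Unadjusted standard error of the log ratio at 400:200: 0.944 × √(1/400 + 1/200) = 0.0818.

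**3. What adjustment is worth.** The documents do not say how much of the log-titre variance the factors explain, so R² is an assumption. The adjusted standard error is about 0.0818 × √(1 − R²). The last column is the true one-sided error of the unadjusted test at nominal 0.01, Φ(−2.326/√(1 − R²)), if allocation balances the factors exactly.

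| R² | Adjusted SE | Reduction | Equivalent gain in sample, 1/(1 − R²) | True error of unadjusted test |
|---|---|---|---|---|
| 0.05 | 0.0797 | 2.5% | 1.05 | 0.0085 |
| 0.10 | 0.0776 | 5.1% | 1.11 | 0.0071 |
| 0.20 | 0.0732 | 10.6% | 1.25 | 0.0046 |

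The unadjusted test therefore errs on the conservative side.

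**4. What sex alone contributes.** Assume half the participants are women and that women's titres are 1.2 to 1.5 times men's. The variance due to sex is 0.25 × (ln 1.2)² = 0.0083 to 0.25 × (ln 1.5)² = 0.0411. That is 0.9% to 4.6% of 0.892, which changes the standard error by 0.5% to 2.3%.

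**5. Imbalance if sex is not stratified.** With half women, the arm difference in the proportion of women has SD √[0.25 × (1/400 + 1/200)] = 0.043, a 95% range of about ±8.5 points. At 30% or 70% women the range is about ±7.8 points. Under the titre ratios in step 4, a difference of 8.5 points moves the geometric mean ratio by a factor of exp(0.085 × ln 1.2) = 1.016 to exp(0.085 × ln 1.5) = 1.035, against a planning ratio of 1.35.

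**The case against.** The strongest reply is that this is a wording slip. Section 6.3 is the operational text, with software, age bands and import route, and the two shorter statements can be read as abbreviations of it. Of the three statements with sex, only section 6.3 ties sex to randomisation in so many words. The planned t-test is valid either way. An adjusted model is a matter of preference that the SAP, not shown here, may already cover.

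Much of this stands. Section 6.3 is the most likely description of the actual list, and validity is not in question. But both shorter statements give what reads as a complete list of factors, and nothing marks them as partial. Section 9.3.2 also names the primary test itself rather than leaving it open, so the choice of an unadjusted test is on the page.

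Two stronger readings are tempting, and the documents support neither:

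- **That the analysis strata are contradictory.** The protocol defines none. Sections 9.3.2 and 9.3.3 give unadjusted comparisons, and no subgroups are planned. What is left unsettled is only which factors an analysis would adjust for.
- **That sex imbalance threatens the primary conclusion, or that a mismatch makes the standard errors anti-conservative.** The imbalance in step 5 is ordinary chance variation, which the test's error rate already allows for. It is not bias. Leaving out a prognostic stratification factor generally makes the standard error too large, not too small. Nor would stratifying by sex guarantee exact balance: the protocol states neither block size nor number of centres, and small cells can leave blocks incomplete.

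**Conclusion.** The contradiction is real: five statements in three sections (1.1, 4.1, 6.3), two without sex and three with it. It cannot be resolved from the text, although section 6.3 is the natural reference. Its direct statistical effect is small. The planned test is valid under either scheme, the sample size is unaffected, and sex alone would change the standard error by about 0.5% to 2.3% under the assumptions in step 4.

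The more useful consequence is that the primary analysis ignores every factor used in randomisation. It is therefore conservative to the extent that centre, age and sex predict titre: about 3% to 11% in the standard error for an assumed R² of 0.05 to 0.20. This is a worthwhile improvement, not a threat to the trial's conclusion.

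**What to change.** 1. Check which factors and age bands define the list actually loaded in REDCap.
2. State that one set, in the same words, in all five places. If section 6.3 is right, this means adding sex to the Randomization entry of the synopsis and to the Randomisation and blinding paragraph of section 4.1.
3. In section 9.3.2, make the primary analysis a linear model of day-14 log titre on arm, adjusted for the factors used in randomisation, pooling small centres by a rule fixed in advance if needed. Report the exponentiated arm coefficient and its confidence limit as the geometric mean ratio. Keep the unadjusted t-test as a sensitivity analysis, and say where the rank test now stands.

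Cost: wording in two to five places, plus a rewrite of the primary analysis paragraph covering test, interval and fallback. The model uses only data collected at entry. Sample size, visits and participants are unaffected. If the SAP already specifies such a model, only the protocol text needs aligning with it.

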| 
Primary immunogenicity endpoint:
 
 
Serological response to vaccination (antibodies against SARS-CoV-2 spike protein) as measured by immunoassay, 14 days after vaccine dose (Group 1) or randomization (Group 2) .
 
 
Secondary immunogenicity endpoint:
 
 
Serological response to vaccination (antibodies against SARS-CoV-2 spike protein) as measured by immunoassay, 28 days after vaccine dose (Group 1) or randomization (Group 2) .
 
SARS-CoV-2 neutralization as measured by virus neutralization assay, 14 and 28 days after vaccine dose (Group 1) or randomization(Group 2) .
 
Serological response to vaccination (antibodies against SARS-CoV-2 spike protein) as measured by immunoassay at 3, 6 and 12months after randomization.
 
Neutralizing antibody titers at 3, 6 and 12 months after randomization.
 
 
Secondary efficacy endpoints:
 
 
The number of participants with molecularly confirmed COVID-19.
 
Presence and severity of COVID-19 signs and symptoms as measured by Symptoms of Infection with Coronavirus-19 (SIC).
 
 
Primary safety endpoints:
 
 
Solicited local and systemic adverse events (AEs) for a period of 7 days after vaccination.
 
Unsolicited local and systemic adverse events (AEs) for a period of 28 days after vaccination
 
Serious adverse events (SAEs) throughout the study (from randomization until end of the study).
 
Medically-attended adverse events (MAAEs) from the day of vaccination until 6 months after the last vaccination.
 
Abnormal laboratory parameters at 1 month visit after COMIRNATY vaccination.
 
 |                                                                                                                                         |

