#### **Safety Analysis:**

All clinical safety data will be listed by participant, time from vaccination dose and treatment arm. Continuous variables will be summarized using sample size (N), mean, standard deviation, median, minimum, and maximum. Frequency counts will be reported for categorical data.

A Data and Safety Monitoring Committee (DSMC) will review data for decisions on arms incorporation and withdrawal and will ensure that the appropriate oversight and monitoring in conducting the clinical trial. Interim analysis could be planned as necessary in each sub-protocol.

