| Solicited local and systemic adverse events (AEs) for 7 days after vaccine. Via E-diary     |                                               |                   |         |         | X (7 days)              |         |         |              |
| Unsolicited local and systemic adverse events (AEs) for 28 days after vaccine . Via E-diary |                                               |                   |         |         | X           |         |         |              |
| Unsolicited SAEs                                                                            |                                               | X                 |         |         |                         |         |         |              |
| Medically-attended adverse events (MAAEs)                                                   |                                               | X                 |         |         |                         |         |         |              |
| Immune response evaluation                                                                  |                                               | X                 | X       | X       | X                       | X       | X       | X            |

Note: If subjects in Group 2 are not crossed over, the visits will be the same as the groups 1.

1. Temperature, blood pressure and heart rate

2. Lab determination could be performed either at screening visit or randomization

3. Two days per week

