| Safety                                                                                                                                                                                                                  |                                                                                                                                                                                                                                                                                                                                                                                                                                                                                                          |
| To evaluate the safety of a dose of COMIRNATY in subjects that received a previous single dose of VAXZEVRIA.                                                                                                                   | 
- Solicited local and systemic adverse events (AEs) for 7 days after vaccine
 
- Unsolicited local and systemic adverse events (AEs) for 28 days after vaccine (Two days per week)
 
- Serious adverse events (SAEs) throughout the study (from randomization until end of the study).
 
- Medically-attended adverse events (MAAEs) from the day of vaccination until 6 months after the last vaccination
 
- Lab parameters: biochemistry and haematology at 1 month visit.
 |

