**Visit 5 (Day 90±10 or 56±3):**

- Inquire about AEs and general well-being of the participant since the administration of vaccine dose. Record any AEs, ‘solicited’ and ‘unsolicited’ AEs, SAEs and MAAE.
- Review medication history
- Measure vital signs (body temperature, pulse, blood pressure).
- Blood extraction for immune response evaluation
- Lab determination at 56±3 for group 2 in case of COMIRNATY vaccination

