### 9.2. Analysis Sets

For the purposes of analysis, the following analysis sets are defined:

| Participant Analysis Set | Description                                                                                                                                                                                                                                                                              |
|--------------------------|------------------------------------------------------------------------------------------------------------------------------------------------------------------------------------------------------------------------------------------------------------------------------------------|
| Full analysis set        | 
 
All participants having received at least one dose of study intervention and who have at least one efficacy evaluation after baseline. Participants will be included in the analyses according to the planned randomized intervention.
 
 |
| Safety analysis set      | 
 
All participants who are exposed to a study intervention. Participants will be analysed according to the intervention they actually received.
 
                                                                                          |

The full analysis set is used to analyse endpoints related to the efficacy objectives and the safety analysis set is used to analyse the endpoints and assessments related to safety.

The following data points sets are defined:

| Defined Data Points Sets | Description                                                                                               |
|--------------------------|-----------------------------------------------------------------------------------------------------------|
| DPS1                     | 
 
All observed data will be included in the analysis set.
 
 |

| Defined Data Points Sets | Description                                                                                                                                                                                                 |
|--------------------------|-------------------------------------------------------------------------------------------------------------------------------------------------------------------------------------------------------------|

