### 9.3. Statistical Analyses

#### 9.3.1. General considerations

All analyses will be carried out using the statistical software SAS, version 9.4 of the SAS system for Windows.

All continuous variables will be summarized using the following descriptive statistics: n (non-missing sample size), mean, standard deviation (SD), 1st quartile, median, 3rd quartile, maximum and minimum. Absolute and relative frequencies (based on the non-missing sample size) of observed levels will be reported for all categorical variables.

All continuous variables will be tested for normality hypothesis assumption with the kolmogorov-Smirnov test. The antibodies binding to the SARS-CoV-2 S protein will be measured as lognormal distribution to obtain more nearly symmetric distribution.

The number of participants and the flowchart of the study will be presented. The period of enrolment and the total number of participants screened to be included in the study will be presented. The number of ineligible participants and the total number of randomized participants will be presented. The number of participants who never receive the study intervention will also be presented by treatment group and those who were included in the full analysis set and the safety analysis set will be presented.

Baseline is considered as the day 1 visit and the baseline data is data collected just before intervention at day 1. Participants with missing baseline value will be excluded from the analysis.

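### The primary laboratory safety endpoint is worded without reference to the pre-dose panel or the unvaccinated arm's Day 28 panel, although both are scheduled

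*Protocol*

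**What the plan says.** **Endpoint.** The primary safety endpoints in the Protocol synopsis (1.1) include "Abnormal laboratory parameters at 1 month visit after COMIRNATY vaccination". Table 3.1 gives the corresponding entry as "Lab parameters: biochemistry and haematology at 1 month visit". The first is tied to COMIRNATY and to abnormal values. The second is tied to neither. No baseline, comparator or threshold appears in either.

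**Schedule (1.2 Flowchart and section 8).** Both groups have a baseline panel, with the footnote "Lab determination could be performed either at screening visit or randomization". Group 1 has a second panel at Visit 4 (Day 28). In the crossover flowchart Group 2 has panels at Visit 4 and Visit 5, and the Visit 5 text explains the later one: "Lab determination at 56±3 for group 2 in case of COMIRNATY vaccination". Without crossover, "If subjects in Group 2 are not crossed over, the visits will be the same as the groups 1", so the Day 28 panel exists in that case too.

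**Analysis set and analysis.** Section 9.2 defines the safety set as "All participants who are exposed to a study intervention" and uses it to present safety data. Section 9.3.5 names only serious adverse events leading to discontinuation and death, and leaves further detail to the SAP. The synopsis adds: "All clinical safety data will be listed by participant, time from vaccination dose and treatment arm". Section 9.3.1 has a general rule: "Baseline is considered as the day 1 visit and the baseline data is data collected just before intervention at day 1".

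**The concern.** A safety endpoint should isolate what changed after the dose. This one is a cross-section about a month after vaccination. A value that was out of range before the dose, or that drifted out of range by ordinary variation, meets the wording as readily as one caused by the vaccine. People in a stable clinical situation are eligible (5.1), so abnormal values before the dose are to be expected.

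The trial has two ways to remove this background: the participant's own pre-dose panel, and a randomized unvaccinated arm sampled on the same day. The endpoint as worded calls on neither, and the safety set, taken literally, removes the second. At stake is whether the laboratory part of the primary safety objective can be read as evidence about the vaccine.

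**Working it through.** The Protocol gives no figure for laboratory abnormalities, so there is nothing to reproduce. The check is mainly textual, followed by an illustration of size.

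**1. How the other endpoints are referenced.** In the synopsis, the Day 14 and Day 28 immunogenicity endpoints run from the dose in Group 1 and from randomization in Group 2. Serious adverse events run from randomization. The statistical part of the synopsis asks for change in immune response from baseline. All of these bring in the control arm or the baseline. The laboratory endpoint does neither.

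**2. Which panels exist.**

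| | Pre-dose or baseline | Day 28 (Visit 4) | Day 56 (Visit 5) |
|---|---|---|---|
| Group 1 | screening or Visit 1 | yes, about 28 days after the dose | no |
| Group 2, crossed over | screening or Visit 1 | yes | yes, about 28 days after the dose |
| Group 2, not crossed over | screening or Visit 1 | yes (Group 1 schedule) | no |

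For crossed-over controls, the one-month post-COMIRNATY panel is the Day 56 one. Their Visit 4 panel therefore falls outside the synopsis endpoint. The Protocol does not say outright that the Visit 4 sample precedes the dose. Section 8 lists the Visit 4 blood and laboratory steps before the control-arm vaccination steps, which suggests that order.

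**3. Size of the background (illustration).** Table 10.2.1 names 13 blood parameters: 5 in haematology (lymphocyte fractions not counted separately) and 8 under clinical chemistry, including INR. Assume no vaccine effect, independent analytes and an out-of-range rate p for each. The documents give no p, so a range is shown.

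P(at least one abnormal) = 1 − (1 − p)^13

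| p | P(at least one) | of 400 in Group 1 | of 200 in Group 2 |
|---|---|---|---|
| 1% | 1 − 0.99^13 = 12.2% | 49 | 24 |
| 2.5% | 1 − 0.975^13 = 28.0% | 112 | 56 |
| 5% | 1 − 0.95^13 = 48.7% | 195 | 97 |

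**4. Would the baseline panel alone be enough?** Take p = 5% and an assumed within-person correlation between baseline and Day 28 of 0.6 to 0.8. Simulation of 200,000 people shows that 25% to 44% of the Day 28 abnormal values were already abnormal at baseline. The rate of newly abnormal values per analyte is then 0.05 × (1 − 0.25) = 0.0375 down to 0.05 × (1 − 0.44) = 0.028. Over 13 independent analytes this gives 1 − 0.9625^13 = 39% down to 1 − 0.972^13 = 31% with a newly abnormal value and no vaccine effect, against 49% without a baseline reference. The baseline removes part of the background. The concurrent unvaccinated arm is needed for the rest.

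**The case against.** The strongest reply is that this is SAP territory. Thresholds, shift tables and displays by arm are commonly left to the SAP, section 9.3.5 defers to it, and it is not shown. The Protocol also has softening elements. Safety data are to be listed by treatment arm. Baseline is defined in general terms. Clinically relevant events between consent and first vaccination are recorded as pre-existing (8.4.1). Appendix 3 lists laboratory adverse events, so these also pass through the adverse-event route.

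Much of this stands for grading and layout. It does not reach the endpoint definition and the safety set, which this document itself states. A listing by arm does not bring in people whom the set leaves out. The 8.4.1 rule concerns clinical events and not out-of-range values at Day 28. Appendix 3 names analytes without tying them to this endpoint. The general baseline rule refers to day 1, whereas the panel may come from screening, and it is not linked to this endpoint.

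The literal reading of the safety set may not be intended. Section 6.1 places the control arm under its heading on interventions administered. The full analysis set has similar wording and must nevertheless contain the controls for the primary comparison. That is a reason to make the text explicit; it does not settle the matter.

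Three stronger readings are tempting and are not supported:
- A reader might infer that every abnormal value will be counted, or that participants will be scored on having any abnormality. The Protocol does not define abnormal and states no counting rule.
- A reader might infer that about half of participants will be flagged. That needs a 5% rate per independent analyte, which is an assumption; at 1% the figure is 12%.
- A reader might infer that the laboratory safety question cannot be answered at all. The data to answer it are scheduled, and nothing forbids their use.

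**Conclusion.** The point holds as a defect in how a primary safety endpoint and its analysis set are worded. The two statements of the endpoint do not match, neither refers to the pre-dose panel or the unvaccinated arm, and the safety set read literally leaves out unvaccinated controls. Followed as written, the endpoint mixes vaccine-related abnormalities with pre-existing and background ones.

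The 12% to 49% range shows that this background could be substantial. It rests on independence, 13 analytes and assumed rates, and does not predict what the trial will report. Positive correlation between analytes would lower the upper figure somewhat, to about 42% to 45% at correlations of 0.3 to 0.2. Chronic disease in the eligible population would tend to raise it.

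The endpoint carries no hypothesis test, alpha or sample size, and the primary immunogenicity comparison is unaffected. The change should be made, but the trial's main conclusion does not depend on it.

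**What to change.** - In the synopsis (1.1) and Table 3.1, use one wording: *new or worsened laboratory abnormalities versus the pre-dose panel at Day 28, by randomized arm*. Report the difference in proportions with a 95% CI.
- State that the pre-dose panel for this endpoint is the screening or Visit 1 sample, so that the day 1 baseline rule in 9.3.1 does not exclude people sampled at screening.
- State that the Group 2 Visit 4 sample is taken before any COMIRNATY dose. Use it as the concurrent control at Day 28, and as the pre-dose panel for the Visit 5 panel of crossed-over controls.
- In 9.2, let Group 2 enter this summary as the no-vaccine arm.

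Grading thresholds may stay in the SAP.

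With 400 and 200 participants and a common proportion q, the 95% half-width for the difference is about 1.96 × √[q(1 − q)(1/400 + 1/200)]. This is 5.6 percentage points at q = 12.2%, 7.6 at 28.0% and 8.5 at 48.7%.

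The cost is endpoint wording and one more table. All samples are already scheduled. The small downside is that participants without a baseline laboratory value drop out of this summary.
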